### **9.3.3 Secondary outcome analysis**

Secondary and exploratory outcome measures will be analysed similarly, using an appropriate generalised linear model, including binary logit regression for dichotomous outcomes (e.g. smoking status) and ordered logit for ordinal outcomes (e.g. alcohol intake). Statistical significance will be at the 2.5% level, consistent with the assumptions made in the sample size calculation. Descriptive summaries of process outcomes will be reported but no formal analysis of these data will be undertaken.

## **9.4. Subgroup analyses**

Compliant with CHAMP reporting guidelines, pre-specified exploratory subgroup analyses for moderators will examine effects of socio-economic status (IMD, perceived wealth; financial strain; education; work status; social weight loss; household and relationship status); mental health and wellbeing (EQ-5D-5L; anxiety and depression dimension of EQ-5D-5L; WEMWBS, disability, a self-report mental health condition, PHQ-4, WSSQ, lives alone, alcohol frequency, possible latent mental health condition and obesity related comorbidity [53], MLTC, presence or absence of diabetes as one of the MLTC); other effects (satisfaction; confidence). See section 4.4.3 and the statistical analysis plan.

The NIHR Funding Board asked for subgroup analysis of outcomes by recruitment centre, strategy (community vs GP) and deprivation category (based on the postcode address where participants live – UK adjusted IMD – e.g. most deprived two quintiles v least three deprived quintiles). Data from the separate IMDs in England, Scotland and Northern Ireland will be combined to account for differences in their methodologies [54]. The context and places where men are recruited will be reported descriptively, removing any identifiable data to maximise protection of participant anonymity, as we did in the Feasibility Study. In the Feasibility Study, participants recruited via GP obesity registers were more likely to live in deprived communities, were older (M=57.1 vs. 48.3 years), more likely to report having a co-morbidity (87% vs. 44%) and had lower BMI (35.0 kg/m^2 vs. 36.2 kg/m^2) compared to community recruits. In addition, there were different 12-month retention rates: (80% GP vs. 71% community), hence we will investigate these differences. Subgroup by treatment group interactions will be tested and all exploratory sub-group and mixed methods analyses will be reported separately from the primary outcome analysis.

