### 4.4.3 Exploratory endpoints/outcomes

**Exploratory endpoints/outcomes at 12 months:** weight management strategies used; self-monitoring activity weight; self-monitoring steps; physical activity; alcohol; smoking; satisfaction with Game of Stones; satisfaction with weight loss progress; confidence in ability to lose weight; confidence in ability to maintain weight loss long term.

**Outcomes at 24 months:** weight change (absolute Kg, %) from baseline and from 12 months. Depending on the advice of the TSC for Phase 3, additional outcomes may be reported (Table 1)

In our Feasibility Study the following were found to be acceptable and feasible to collect high quality data: physical activity [18]; alcohol consumption [19]; smoking status [20]; satisfaction with interventions (Feasibility Study tool); Warwick-Edinburgh Mental Well-Being Scale (WEMWBS) [21] and weight management strategies used over last 12 months. This question has been adapted by Co-Investigator [name] from the top 10 effective strategies adapted from Hartmann-Boyce (2016) Oxford Food and Activity Behaviours (OxFAB) Cohort Study [22]. [name] has used this in a recent survey of 1000 men with obesity in Canada (unpublished –in progress).

**Process outcomes:** incentives gained; weight change (absolute, %) at 3 and 6 months; number and chosen frequency of SMS delivered; any responses to SMS; web page use; recruitment and retention

by recruitment strategy, health inequalities: perceived wealth[23]; financial strain[24, 25] to explore the UK cost of living crisis unfolding during this trial.

Qualitative interview data with men at 12 and/or 24M will generate findings which will help to understand experiences and behaviours of men during and after the interventions and barriers/facilitators to longer term sustained weight loss and scalability of the intervention.

Addressing health inequalities, mental health and multiple long-term conditions (MLTC) are key government priorities, together with understanding the mediators and moderators for weight management. These are all inter-related and casual pathways are complex and multi-directional.

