A parallel integrated mixed methods exploratory analysis will be conducted for weight change (%) focusing on the quantitative subgroup analyses described in 9.4 for 1) socio-economic status 2) mental health and wellbeing 3) co-morbidity and multiple long-term conditions (with and without diabetes); other effects (satisfaction, confidence in ability to lose weight and maintain weight loss). We will measure mental health and wellbeing using a range of validated questionnaires to inform a multi-lens approach moderator analysis. This is important to address the complexity of experiences reported by men involved in our feasibility study, PPI feedback, the diverse recruitment strategies and to maximise knowledge around health inequalities. MLTC is defined as the co-existence of two or more chronic conditions where obesity is a recognised risk factor - stroke including mini-stroke, high blood pressure, a heart condition, diabetes, cancer, arthritis, mental health problem or self-report disability (ONS standardised definition). Obesity is a risk factor for MLTC but is not currently classified as a disease and will not be included. More detail is provided in Section 9.

Table 1. Table of endpoints/outcomes

Outcome assessment schedule according to STAR-LITE core outcome set [17], obesity programmes checklist from the Men's Health Forum [26] and Feasibility Study findings [2].

| Data Collection                                                                                                                                                   | *0M | 12M | **24M |
|--------------------------------------------------------------------------------------------------------------------------------------------------------------------------|------------|------------|--------------|
| Socio-demographic: IMD, co-morbidities (physical and mental health), self-report disability, ethnicity, age, education, employment, household size; relationship status. | ✓          |            |              |
| Perceived wealth, financial strain                                                                                                                                       | ✓          | ✓          | ✓            |
| Anthropometry - height (for BMI)                                                                                                                                         | ✓          |            |              |

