| Anthropometry – weight                                                                                                                                                   | ✓          | ✓          | ✓            |
| Participant satisfaction                                                                                                                                                 |            | ✓          | ✓            |
| Health behaviours - physical activity, smoking status, alcohol frequency                                                                                                 | ✓          | ✓          |              |
| Weight management strategies used over last 12 months                                                                                                                    | ✓          | ✓          | ✓            |

|                                                                                                                                                        |   |   |   |
|--------------------------------------------------------------------------------------------------------------------------------------------------------|---|---|---|
| Confidence in ability to lose weight and maintain weight loss                                                                                          | ✓ | ✓ | ✓ |
| PHQ-4                                                                                                                                                  | ✓ | ✓ |   |
| EQ-5D-5L – Anxiety and Depression Dimension (AD)                                                                                                       | ✓ | ✓ |   |
| Warwick-Edinburgh Mental Well-Being Scale (WEMWBS)                                                                                                     | ✓ | ✓ |   |
| Weight Self-Stigma Questionnaire (WSSQ) (included in SWAT PhD)                                                                                         | ✓ | ✓ |   |
| Health Economic Outcomes: EQ-5D, NHS health care use; public sector weight management services                                                         | ✓ | ✓ | ✓ |
| Qualitative interview data (experiences, behaviours)                                                                                                   |   | ✓ | ✓ |

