| Process outcomes: observed weight meets target and incentives secured/lost at 3M and 6M; number of SMS delivered; SMS responses, web page use over 12M | ✓ | ✓ |   |
| Unintended consequences or adverse events                                                                                                              |   | ✓ | ✓ |

\*OM = Baseline i.e. pre-randomisation; \*\*Phase 3 of trial guided by Trial Steering Committee

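### Section 9.4 lists satisfaction, which is measured only after randomisation, as a moderator of the treatment effect

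*Protocol*

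**What the plan says.** Protocol section 9.4 opens by stating that "pre-specified exploratory subgroup analyses for moderators will examine effects of socio-economic status" and then runs through several groups of variables. The last group in that same sentence is "other effects (satisfaction; confidence). See section 4.4.3 and the statistical analysis plan". The section closes with the test to be applied: "Subgroup by treatment group interactions will be tested".

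The measurement schedule is Table 1 in section 4.4.3. The row "Participant satisfaction" is ticked at 12M and 24M and blank at 0M. The footnote defines 0M as "Baseline i.e. pre-randomisation".

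Section 4.4.3 names the items among the exploratory outcomes at 12 months: "satisfaction with Game of Stones; satisfaction with weight loss progress". Its later paragraph on the mixed-methods analysis of percentage weight change mentions "other effects (satisfaction, confidence in ability to lose weight and maintain weight loss" after three numbered domains. It gives no baseline version of satisfaction.

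The baseline variables in section 9.3.1 include confidence but not satisfaction.

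**The concern.** A moderator has to be fixed before randomisation. Only then are the men compared within a level of it still randomised groups, and only then does the interaction say for whom the treatment works better.

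Satisfaction fails this on two counts. First, one item asks about weight loss progress and is collected at the 12-month assessment, when the primary outcome is measured, so splitting on it partly sorts men by that outcome. Second, the other item asks about the programme, and the programme differs by arm. Under section 7.2, controls wait 12 months for text messages, have no weight targets and no self-monitoring page. A satisfied control and a satisfied man in an intervention arm have been selected in different ways.

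At stake is one exploratory result. It could show a diluted effect in every stratum, or an interaction where none exists. Section 9.3 says the exploratory subgroup analyses are meant to inform future research and implementation, and this one could not do so.

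**Working it through.** **1. The plan's own figure.** The protocol gives no figure for this analysis. The sample size in section 9.1 supplies the scale and does reproduce: n = 2 × (2.2414 + 1.2816)² × (8/3.3)² = 2 × 12.41 × 5.877 = 145.9, so 146 per group. Then 146/0.75 = 194.7, so 195 per group, and 3 × 195 = 585. Nothing below affects it.

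**2. Timing, side by side.**

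| Variable | Listed in the 9.4 moderator sentence | 0M in Table 1 | 12M | 24M | In the 9.3.1 baseline list |
|---|---|---|---|---|---|
| Satisfaction | yes | no | yes | yes | no |
| Confidence | yes | yes | yes | yes | yes |

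Satisfaction has no pre-randomisation value anywhere in the protocol, so the 9.4 analysis can only be run on a post-randomisation one. Confidence has a baseline value. This step settles the point; the arithmetic that follows only illustrates direction and possible size.

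**3. Illustration: set-up.** One intervention arm against control, with the same true effect in every man.

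- From section 9.1: effect 3 percentage points; SD 8 kg/109 kg = 7.3%.
- Assumed, because the documents give nothing: mean loss 1% in control and 4% in intervention; correlation r of 0.3, 0.5 or 0.7 between satisfaction and weight loss; a direct arm shift d in satisfaction of 0 or 0.3 SD; a cut-off c at 0 or 0.8 SD higher.
- Latent satisfaction: S = r(Y − 2.5)/7.3 + √(1 − r²)·e + d (d in the intervention arm only). Its within-arm variance is 1.

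With z₁ = c − (r × 1.5/7.3 + d) for intervention and z₀ = c + r × 1.5/7.3 for control, the truncated-normal means give

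- satisfied stratum: 3 + 7.3r[φ(z₁)/(1 − Φ(z₁)) − φ(z₀)/(1 − Φ(z₀))]
- dissatisfied stratum: 3 − 7.3r[φ(z₁)/Φ(z₁) − φ(z₀)/Φ(z₀)]

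Worked case, r = 0.7, d = 0.3, c = 0.8: z₁ = 0.356 and z₀ = 0.944. Satisfied: 3 + 5.11 × (1.038 − 1.480) = 0.74. Dissatisfied: 3 − 5.11 × (0.586 − 0.309) = 1.58. Interaction: −0.85.

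**4. Illustration: results** (percentage points; the true effect is 3.0 in both strata and the true interaction is 0).

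| Cut-off | Arm shift | r | Satisfied | Dissatisfied | False interaction |
|---|---|---|---|---|---|
| 0 | 0 | 0.3 | 2.83 | 2.83 | 0.00 |
| 0 | 0 | 0.5 | 2.52 | 2.52 | 0.00 |
| 0 | 0 | 0.7 | 2.07 | 2.07 | 0.00 |
| 0 | 0.3 | 0.3 | 2.44 | 2.38 | +0.06 |
| 0 | 0.3 | 0.5 | 1.89 | 1.77 | +0.12 |
| 0 | 0.3 | 0.7 | 1.20 | 1.00 | +0.20 |
| 0.8 | 0 | 0.3 | 2.79 | 2.88 | −0.09 |
| 0.8 | 0 | 0.5 | 2.42 | 2.68 | −0.26 |
| 0.8 | 0 | 0.7 | 1.86 | 2.37 | −0.51 |
| 0.8 | 0.3 | 0.3 | 2.30 | 2.56 | −0.26 |
| 0.8 | 0.3 | 0.5 | 1.61 | 2.13 | −0.52 |
| 0.8 | 0.3 | 0.7 | 0.74 | 1.58 | −0.85 |

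At r = 0 every entry is 3.0 and the interaction is 0. Simulation of the same model gives the same values to within 0.03 points. A separate simulation on the kg scale (3.3 kg, SD 8 kg, arm shift up to 0.5 SD) gave false interactions of up to about −1.5 kg, so the size follows the assumptions.

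**The case against.** Four arguments count against making much of this.

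- **The label may mean outcomes.** In 4.4.3, satisfaction and confidence stand after the three numbered domains and can be read as further outcomes in the mixed-methods work; 9.4 refers back to that text. This stands for 4.4.3, so a reader should not infer that 4.4.3 contains a second moderator list. It does not rescue 9.4, where satisfaction sits inside the moderator sentence and interaction tests follow.
- **Confidence might seem to share the fault,** since 9.4 names no time point for it. It does not: Table 1 collects it at 0M and 9.3.1 lists it at baseline. Stating which value enters the model is detail for the SAP.
- **The illustration mostly shows shrinkage within strata, while the planned test is the interaction.** This stands. Split at 0, the false interaction is at most about 0.2 points; a larger one needs a cut-off away from the centre. The correlations, arm shift and cut-offs are all assumed.
- **The analysis is exploratory and separate.** Sections 9.3, 9.4 and 12.1 call these analyses hypothesis generating or report them apart from the primary result. A reader might infer that the trial's main conclusions, or commissioners' decisions, are at risk. The documents do not support that: section 3.1 says commissioners want variation by socio-economic group and co-morbidity, and does not mention satisfaction.

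The SAP is not shown and may treat satisfaction differently. The protocol would still name a post-randomisation outcome as a moderator and need correcting.

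**Conclusion.** Section 9.4 is wrong as written on one variable. Satisfaction has no value before randomisation, is partly a consequence of the primary outcome and of the allocated arm, and cannot serve as a moderator. This conclusion rests only on the protocol's list and its schedule.

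The size is not known. Under the stated assumptions, a constant 3-point effect appears as about 2.8 to 1.0 points within strata split at 0. The false interaction is up to about 0.2 points there, and from about −0.1 to just under −0.9 points with the higher cut-off. These figures show direction and plausibility and are not an estimate for this trial.

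The damage is confined to one exploratory, separately reported analysis. The sample size and the primary, secondary, economic and progression analyses are unaffected, and the finding does not extend to confidence.

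**What to change.** Delete satisfaction from the moderator list in section 9.4. Keep it as a 12-month exploratory outcome, compared between arms under section 9.3.3, and in the process evaluation. In the mixed-methods paragraph of section 4.4.3, add a clause saying that satisfaction is an outcome there and not a subgroup variable. If the SAP repeats the 9.4 list, make the same deletion.

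The cost is a wording change and the loss of one exploratory interaction test. Data collection, sample size and timetable stay as they are.

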## **9.5. Interim analysis and criteria for the premature termination of the trial**

This is an automated self-care intervention and there are unlikely to be any safety concerns (there were none in the Feasibility Study) and neither is cross-over a concern as the intervention delivery is automated. Given the low-risk nature of the intervention, it has been agreed with the Sponsor that an independent data monitoring committee will not be required and therefore no interim analyses will be conducted.

## **9.6. Participant population**

The participant population for statistical analysis is all participants randomised (intention to treat).

## **9.7. Procedure(s) to account for missing or spurious data**

For all baseline characteristics and outcome measures, we will report the level of missing data. When estimating treatment effects, if a relevant baseline score is missing, we will implement best practice by imputing the score (if continuous) or adding an extra category for missing (if categorical). The primary analysis will use multiple imputation of missing outcome data, applying predictive mean matching. Sensitivity analyses of the primary outcome will examine the data under various assumptions around missingness, including an analysis of observed cases only, in addition to missing weight data being treated as Baseline Observation Carried Forward (BOCF) (which in our 12-month assessment is the same as a Last Observation Carried Forward (LOCF)), as recommended in the STAR-LITE core outcome set [17], for comparability with previous weight loss studies [55].

Data quality assurance and source data verification will be carried out in accordance with the CTU's standard operating procedures in order to minimise spurious data. Further data quality checks will be carried out by the trial statistician prior to the analysis and potentially implausible data will be queried with trial office and/or site staff.

If a data item includes the option "Prefer not to say", any such responses will be treated as a separate category and not classed as missing data.

## **9.8. Other statistical considerations.**

The final approved version of the Statistical Analysis Plan will be publicly available at the end of the trial. This will be accompanied by a summary of changes made from the original version and the final approved version. We will also report any aspects of the analysis which have deviated from the SAP along with a justification for the deviation.

One other consideration is that the TSC in discussion with NIHR may consider other core outcome criteria in addition to the primary outcome when deciding about progression to Phase 3. This will include the following secondary outcome measures: absolute weight change (kg); % of participants achieving  $\geq 5\%$  weight loss; % of participants achieving  $\geq 10\%$  weight at 12M from baseline.

## **9.9. Economic evaluation**

A full economic evaluation will be conducted. This will include a trial-based analysis and a decision model to assess economic value over an extrapolated lifetime horizon. The primary economic outcome

will be incremental cost per Quality Adjusted Life Year (QALY). A Cost Effectiveness analysis (incremental cost per % weight loss) will also be performed. Firstly, these analyses will be performed using the 12M follow-up data, then updated if the study progresses to Phase 3 (24M follow-up).

**Estimation of costs:** The resources associated with the interventions will be measured using study-specific forms. Other NHS resource-use (GP, nurse, emergency department, outpatient appointments and inpatient stays) will be collected via participant reported questionnaires at baseline, 12 and 24M. The costs of NHS/Public Health funded weight loss services will also be included. Resource use estimates will be combined with unit costs obtained from standard sources or study specific estimates. Incremental costs (NHS perspective) will be estimated using generalised linear models with appropriate distributions for cost data and adjustment for baseline covariates.

**Estimation of benefits:** We will measure benefits in terms of QALYs gained, based on participant responses to the generic EQ-5D-5l health related quality of life measure at baseline, 12 and 24M if the study progresses to Phase 3. Incremental QALYs will be estimated using generalised linear models with adjustment for baseline covariates.

**Trial based economic evaluation:** Costs and benefits will be combined to estimate cost per QALY gained over the 12M follow up period. A full incremental analysis will be performed. A cost per % weight loss will also be estimated. Deterministic sensitivity analyses will be undertaken to test the impact of assumptions and analysis methods on results. Results will be plotted on cost-effectiveness planes to illustrate the impact of sampling uncertainty on results. The analysis will be updated if the study progresses to Phase 3.

**Longer term cost-effectiveness:** The trial results at 12M will be extrapolated over a life-time horizon using the PRIMETIME-CE-obesity model [56]. This is a proportional, multistate life table population model which links BMI to mortality and a range of diseases including diabetes, coronary heart disease, stroke and cancer. Different assumptions of weight regain will be explored. Differences in Costs and QALYs will be presented for different time horizons (this will include estimates of any cost savings in NHS health care utilisation in the short, medium and long term) although we note that lifetime horizon is the most appropriate for decision making. Sensitivity analyses will explore the impact of other key assumptions on cost-effectiveness. A probabilistic sensitivity analysis and various threshold and scenario analyses will be conducted. Results will be presented on the cost-effectiveness plane and cost-effectiveness acceptability curves used to illustrate the probability that SMS+I and SMS groups are associated with positive or negative incremental net benefit. The model will be updated if the study progresses to phase three.

